### Control arm

Participants in the control arm will have interrupted fascial closure with either 0 vicryl or 0 PDS suture, also termed ‘J-vicryl’ or ‘J-PDS’. As for the intervention arm, the number of interrupted sutures required to close the fascial incision will depend on its size and at the discretion of the operating surgeon to achieve a robust closure free of palpable defects. Bites should be placed approximately 5 to 10 mm from the facial edge and 5 to 10 mm apart. The number of throws will be at the discretion of the operating surgeon. Skin closure and skin dressings or glue will be conducted in the same manner as the intervention group.

### Participant timeline (Table 1) and baseline data

**Table 1 Tab1:**
[figure not shown]
Scheduled and unscheduled visits with timepoints for data collection

Data will be recorded using electronic case report forms (eCRFs) on a secure web-based system (Project REDCap, Vanderbilt University, TN, USA). These consist of baseline demographics, medical history, treatment group, operative details, and primary and secondary outcomes. Follow-up timepoints are 3 months, 1 year and 2 years after the index operation. Additionally, patients requiring inpatient admission will be reviewed by a researcher before discharge for wound events as defined previously.

Baseline demographic data includes age, gender, smoking status, and previous abdominal surgery. Medical history includes history of diabetes, active malignancy, medications affecting healing (chemotherapy, steroids, biologics), ASA grade and comorbidities. Operative details include responsible consultant, pre-operative antibiotics, laparoscopic operation, length of procedure, CDC wound classification, and material used for skin closure.

### Three-month follow-up

Participants are contacted by telephone to arrange a suitable time to visit the outpatient clinic. Information gathered will include length of hospital stay, readmissions within 90 days, return to theatre within 90 days, SSO within 90 days and QoL using modified versions of validated questionnaires. Furthermore, participants will have physical and ultrasound examinations performed by a trained sonographer for the presence of TSH. In this trial, imaging is the definitive modality for detecting the primary outcome. The precise extent (in mm) of any defect, if present, will be recorded, as will whether there is any hernia through this. If so, the width and craniocaudal diameter of the hernia sac will be recorded, along with the presence of any content beyond fat.

### One-year and 2-year follow-up

Data collected at these timepoints are QoL scores and presence of TSH. Ultrasound examination will be performed by the same sonographers who remain blinded to the participant treatment arm. Patients with confirmed TSH detected before the primary endpoint of 2 years are offered ongoing follow-up to monitor TSH size and continued QoL assessment.

### Sample size

This study will be powered for detecting a difference in the primary outcome between groups. Previous prospective studies with similar follow-up duration record an incidence of trocar-site hernia in the region of 25% [7–9]. An absolute reduction in primary outcome of 15% is expected within the intervention group, down to an occurrence of 10%. The best available evidence comes from a systematic review of Duramesh implantation for laparotomy and ventral hernia repair with a median incisional hernia rate of 3.4% after 1 year [13]. An occurrence of 10% was selected as a conservative estimate of the effect size in the intervention group after 2 years. Therefore, using a significance level of 5% and power of 80%, it is calculated that 100 patients per group, 200 in total, are required. After factoring in a 20% rate of loss to follow-up, a total of 250 participants will be included in the trial.

### Recruitment

Potential participants will be selected from local elective, expedited or emergency pathways. Theatre lists will be screened daily for eligible patients undergoing laparoscopic surgery. Patients will be sent participant information leaflets in advance where possible. Informed consent will be obtained on the day of surgery by a member of the research team. A prospective screening log of patients not eligible or who declined participation will be maintained to monitor selection bias.

### Randomisation

Patients will be randomly allocated to either the intervention or control arm when they arrive in the anaesthetic room before knife to skin. The randomisation sequence was generated and is held by the trial statistician. Randomisation and assigning the intervention are performed by the operating consultant surgeon using a secure web-based system (sealedenvelope.com, Sealed Envelope Ltd., London, UK) ensuring allocation concealment. Following statistical advice, the computer-generated randomisation sequence (in 1:1 ratio) will use a block size of 4 and stratify according to BMI (≥ 30 or < 30) and diabetes (present or absent). The operating consultant surgeon will then close the trocar site with the material specified by the allocation arm.

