### Eligibility criteria

Inclusion criteria are adults 18 or older; able to provide informed consent without barriers that might prevent follow-up; and any laparoscopic procedure requiring periumbilical incision for trocar insertion ≥ 10 mm, elective or emergency, pertaining to the domain of general surgery. Acceptable situations include extraction sites up to a maximum of 3 cm, concurrent umbilical hernia if the defect is small enough to accommodate the camera port, and previous abdominal surgery except for the condition specified in the exclusion criteria below.

Exclusion criteria at screening are lack of capacity to provide informed consent; planned open operation; procedures where placement of periumbilical trocar < 10 mm is planned; periumbilical trocar insertion not planned or not possible; specimen extraction site at the umbilicus exceeds 3 cm; use of planar mesh to cover the periumbilical trocar site; previous planar mesh covering the periumbilical trocar site; previous abdominal surgery, if in the opinion of the Principal Investigator, is not suitable for inclusion, e.g. ‘battlefield’ abdomen, enterocutaneous fistulae, multiple previous laparotomies etc.; CDC wound class 4; pregnancy; and body mass index (BMI) ≥ 40.

For elective and expedited surgery, patients fulfilling inclusion criteria and not meeting exclusion criteria will be offered the opportunity to participate in advance by researchers screening operating lists. Patients undergoing emergency surgery will be offered the opportunity to participate by the consultant surgeon on call when the decision for laparoscopic surgery is declared.

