### Blinding

Both participants and outcome assessors are blinded to the treatment arm during the entire study period. By definition, surgeons performing the operation cannot be blinded. To avoid bias, operating surgeons will not be involved in outcome data collection and will be instructed not to reveal the group allocation to researchers or the patients themselves. In addition, they will be instructed not to specify the closure method in the operative records, instead documenting that the fascia was closed according to the TROCAR trial protocol. All other intraoperative and postoperative details will be recorded as usual. Access to data on REDCap will be limited based on blinded, unblinded and administrator roles.

An emergency unblinding process will be available at all hours of the day. Consultant surgeons are permitted to request an emergency unblinding following direct discussion with the Principal Investigator. Unblinding rates will be logged and checked throughout the trial by the research team and Data Monitoring Committee.

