### Loss to follow-up

Our sample size calculations have factored in a 20% rate of loss to follow up, which is based on other studies in surgical populations requiring 2-year follow-up with imaging to detect incisional hernia [19, 20]. By consenting to participate, patients are consenting to the intervention, assessments, follow-up and data collection. Study participants are free to withdraw at any time.

Participants may be withdrawn from the trial by the research team if continued participation is no longer in their best interests. Reasons for discontinuing may include the following: intercurrent illness making data collection impossible, persistent non-compliance with protocol requirements hampering and/or biasing data collection, participant fulfils any of the intra-operative exclusion criteria, and participant loss to follow-up (e.g. moves abroad/not contactable).

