### Integrity of data collection

Designated members of the research team will be responsible for data entry at different steps of the patient pathway. All researchers are trained to ensure the accuracy of the relevant outcome and will ensure that entries can be verified by the source data. Data will be collected pseudonymously and managed using Research Electronic Data Capture (REDCap) hosted by University College London (UCL). REDCap is a secure web-based software platform designed to support data capture for research studies on bespoke electronic case report forms (eCRFs). Unblinded research staff will deal with randomisation and per protocol operating, whereas blinded research staff will collect baseline information and primary and secondary outcome data.

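### Withdrawal for intra-operative exclusion criteria, after an unblinded surgeon has randomised before incision, can take randomised patients out of the primary analysis

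*Protocol article*

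**What the plan says.** Four parts of the protocol article bear on this point.

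- **Randomisation and Blinding.** Allocation precedes the operation: "Patients will be randomly allocated to either the intervention or control arm when they arrive in the anaesthetic room before knife to skin". The person who allocates is the person who operates: "Randomisation and assigning the intervention are performed by the operating consultant surgeon". That person then knows the arm throughout: "By definition, surgeons performing the operation cannot be blinded".
- **Eligibility criteria.** The exclusions are introduced as screening criteria, but the list includes "periumbilical trocar insertion not planned or not possible" and "specimen extraction site at the umbilicus exceeds 3 cm; use of planar mesh to cover the periumbilical trocar site".
- **Loss to follow-up.** Among the reasons for which the research team may discontinue a participant is "participant fulfils any of the intra-operative exclusion criteria".
- **Statistical methods.** The analysis is called intention-to-treat, but the primary analysis uses only randomised participants whose data are not missing. Multiple imputation appears as a sensitivity analysis.

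Protocol deviations adds that major deviations leave the per-protocol set only. It does not mention participants who meet an intra-operative exclusion criterion.

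**The concern.** An intention-to-treat comparison is protected because nothing that happens after allocation can decide who is counted. Here something can. A criterion that is met in theatre, partly through choices made by a surgeon who knows the arm, opens the way to withdrawal. A participant withdrawn on that day will normally have no ultrasound result, and the primary analysis then omits them.

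Two features make this more than a formality. First, the removed patients are unlikely to be average: Background and Discussion both say that larger incisions herniate more often. Second, a difference between arms is plausible, though not shown. Discussion notes that Duramesh comes only with a half-circle needle, which makes placement harder through deep subcutaneous fat, while the control suture is the J type. A surgeon who knows the arm could have an arm-specific reason to handle access or closure differently. Blinded sonography cannot repair a selective loss that has already happened. At stake is the validity of the primary comparison.

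**Working it through.** **1. The plan's own sample size.** Inputs from Sample size: 25% versus 10%, 5% significance, 80% power, 20% loss. Tests are two-sided (Statistical methods). With pooled variance and mean risk 0.175:

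n per arm = [1.96 × √(2 × 0.175 × 0.825) + 0.8416 × √(0.25 × 0.75 + 0.10 × 0.90)]² / 0.15² = 99.5, rounded up to 100.

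Total = 200 / (1 − 0.20) = 250. Both stated figures reproduce, so the sample-size arithmetic is not at issue.

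**2. The order of events.**

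| Step | Where stated |
|---|---|
| Arm allocated by the operating surgeon before incision | Randomisation |
| Incision extended where the specimen requires it | Standardisation |
| Extraction size, unplanned mesh or failed port placement becomes known | Follows from Eligibility criteria and Standardisation |
| Research team may withdraw the participant | Loss to follow-up |
| Participant without outcome data left out of the primary analysis | Statistical methods |

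Each provision is in the text. The last link, that a participant withdrawn in theatre is lost from the primary analysis, comes from reading the last two sections together.

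**3. Size of the bias (assumed inputs).** The documents give no rate of intra-operative exclusion and no hernia risk for such patients. Let p be the true risk in both arms (no treatment effect), e the fraction removed from one arm only, and r the risk among those removed. The observed risk in the thinned arm is (p − e·r)/(1 − e), and the false difference is p minus that value. Take p = 0.25, the protocol's control risk, and r = 0.40:

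- e = 0.05: (0.25 − 0.02)/0.95 = 0.2421, a false difference of 0.8 points.
- e = 0.10: (0.25 − 0.04)/0.90 = 0.2333, a false difference of 1.7 points.

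**4. Range and effect on the test.** Take 100 analysed in the intact arm and 100(1 − e) in the thinned arm. With d the false difference and p′ the thinned-arm risk, SE = √[p′(1 − p′)/(100(1 − e)) + 0.25 × 0.75/100], and the two-sided type I error is Φ(−1.96 + d/SE) + Φ(−1.96 − d/SE).

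| Removed from one arm | Risk in those removed | False difference (points) | Type I error |
|---|---|---|---|
| 5% | 35% | 0.5 | 5.1% |
| 5% | 40% | 0.8 | 5.2% |
| 5% | 50% | 1.3 | 5.5% |
| 10% | 35% | 1.1 | 5.4% |
| 10% | 40% | 1.7 | 5.8% |
| 10% | 50% | 2.8 | 7.4% |

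**5. The benign case.** If the same fraction, at the same risk, is removed from both arms, both observed risks fall equally and the false difference is zero. The whole effect in step 3 comes from removal that depends on the arm.

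**The case against.** The case on the other side is substantial, and part of it stands.

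- **Removal is permitted, not required.** The text says participants may be withdrawn, and by the research team rather than the surgeon. No sentence states that such patients leave the intention-to-treat set, and multiple imputation could bring them back in a sensitivity analysis. This stands as a limit. It does not close the gap, because the primary analysis still omits missing outcomes.
- **Several criteria can be known beforehand.** Discussion says most colectomies and anterior resections will be excluded because the port site is customarily extended; mesh can be planned; wound class 4 can sometimes be foreseen. This stands. The concern is limited to what emerges in theatre, and mainly to extraction size and unplanned mesh, where the surgeon has discretion.
- **The full protocol may hold a separate intra-operative list.** It may, and its absence from the article is no fault. Whatever the list contains, criteria applied in theatre are applied after allocation.

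A reader might also infer more than the documents support:

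- **That the 80% power is lost.** The withdrawal reason sits in the same section as the 20% allowance, which may already count it, and no rate is given.
- **That conversion to open surgery removes patients.** Only a planned open operation is listed as an exclusion.
- **That the fixed block of 4 lets surgeons predict allocations.** That would need knowledge of earlier allocations, which twelve randomising surgeons and four strata make hard to hold, and it is a different issue from post-randomisation withdrawal.

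**Conclusion.** The concern holds in a limited form. The article allows a randomised participant to be withdrawn on grounds that may arise in theatre after an unblinded surgeon knows the arm, and its primary analysis then omits that participant if no outcome is recorded. The patients most exposed include those with larger incisions, whose hernia risk the article itself calls higher.

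The likely size is modest: about 0.8 to 1.7 points under the central assumptions (25% true risk in both arms, 5% to 10% removed from one arm only, 40% risk among those removed), against a design difference of 15 points. The direction is unknown, since either arm could be thinned, and the bias vanishes if removal does not depend on the arm. None of the assumed inputs comes from the documents. The point does not show that bias will occur; it shows that the plan leaves open a route to bias that is cheap to close.

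**What to change.** 1. In Loss to follow-up, delete the meeting of an intra-operative exclusion criterion as a reason for withdrawal.
2. In Statistical methods, state that every randomised participant, including one who meets such a criterion, is followed to 2 years with ultrasound unless consent is withdrawn, and is analysed as allocated. Name these cases as excluded from the per-protocol set only, since the present definition of major deviations does not cover them.
3. Reconcile the screening label in Eligibility criteria with the intra-operative criteria named in Loss to follow-up.
4. Fix in advance, identically for both arms, how the outcome is recorded where no periumbilical port was placed.

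The cost is an amendment and follow-up visits for what may be few patients. The statistical price is a slight dilution of the effect from those who did not receive the allocated closure.

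The sponsor may also consider randomising just before fascial closure. Integrity of data collection already says "Unblinded research staff will deal with randomisation and per protocol operating", which would itself need squaring with the surgeon's role under Randomisation. This is an option, not a required change: recruitment began in June 2025, and moving the point of randomisation now would mix two enrolment points in one analysis.

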## Methods

### Study design

TROCAR is a single-centre, parallel arm, double-blind randomised controlled trial. The study objective is to assess whether Duramesh is superior to conventional slowly absorbable suture (also known as J-vicryl or J-PDS) for closing laparoscopic periumbilical trocar sites 10 mm or greater.

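### A single fixed block size of 4, published during planned recruitment, makes up to one in three allocations deducible by anyone who knows a stratum's full history; emergency patients are most exposed

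*Protocol article*

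**What the plan says.** The Study design section states: "TROCAR is a single-centre, parallel arm, double-blind randomised controlled trial". Under Randomisation, the computer-generated 1:1 sequence "will use a block size of 4" and is stratified by BMI (two levels) and diabetes (two levels), which gives four lists. No variation in block size is described. The trial statistician holds the sequence. The section adds: "Randomisation and assigning the intervention are performed by the operating consultant surgeon", through a web system that is said to secure allocation concealment. This happens in the anaesthetic room, before the incision.

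Other sections bear on who could use knowledge of the sequence:

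- **Setting:** ten consultants and two associate specialists randomise, so twelve surgeons share the four lists.
- **Blinding:** surgeons cannot be blinded. They are told not to disclose allocations to researchers or patients; other surgeons are not mentioned.
- **Eligibility criteria:** emergency patients are "offered the opportunity to participate by the consultant surgeon on call". Elective and expedited patients are approached by researchers who screen operating lists.
- **Recruitment:** a research team member takes consent on the day of surgery. A prospective log of ineligible and declining patients is kept to watch for selection bias.
- **Integrity of data collection:** "Unblinded research staff will deal with randomisation and per protocol operating".
- **Trial status:** recruitment opened in June 2025 and is expected to finish by December 2026.

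**The concern.** A web system hides the next code. It does not stop anyone from working that code out when the block size is known and the earlier allocations in the stratum have been seen. Both stratification factors can be known before randomisation, all surgeons draw on the same four lists, and the surgeons see what they are allocated. The article's assurance about concealment is therefore stronger than the design supports.

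At stake is selection before randomisation. A person who knows or suspects the next arm could offer the trial selectively, or leave a consented patient unrandomised, according to perceived hernia risk. Neither intention-to-treat analysis nor blinded ultrasound can undo this. The screening log, as worded, would not show eligible patients who were never offered the trial, or those who consented but were not randomised.

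**Working it through.** The article gives no figure for predictability, so there is none to reproduce. The inputs are block size 4, ratio 1:1 and four strata (Randomisation), twelve surgeons (Setting) and 250 participants (Sample size).

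**1. Certain knowledge with full history.** A 1:1 block of 4 has 6 equally likely sequences. An allocation is forced once one arm has used both its places.

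- Positions 1 and 2: never forced.
- Position 3: forced if the first two are the same, which is 2 of 6 sequences = 1/3.
- Position 4: always forced.

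Share forced = (0 + 0 + 1/3 + 1)/4 = 1/3 = 33.3%. Over a whole trial of 250 the ceiling is 250/3 ≈ 83 allocations.

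**2. Best guess with full history.** The chances of guessing correctly at positions 1 to 4 are 1/2, 2/3, 2/3 and 1. The mean is (0.500 + 0.667 + 0.667 + 1)/4 = 70.8%, against 50% by chance.

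**3. Partial knowledge.** Assume that each earlier allocation is known independently with probability k and that the position in the block is known. Certainty needs both allocations of the exhausted arm to be known, which has probability k². Share certain = (k²/3 + k²)/4 = k²/3.

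| k | Share certain in advance |
|---|---|
| 1 | 33.3% |
| 0.75 | 18.8% |
| 0.5 | 8.3% |
| 0.25 | 2.1% |
| 1/12 (own cases only, equal caseloads) | 0.2% |

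**4. Alternatives.** Results are for an observer who knows all earlier allocations in the stratum. For the mixtures, the observer also knows which sizes are in use but not their order (simulation, 62 allocations per stratum, since 250/4 = 62.5).

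| Blocks | Certain | Best guess correct |
|---|---|---|
| Fixed 4 | 33.3% | 70.8% |
| Fixed 6 | 25.0% | 68.3% |
| Fixed 8 | 20.0% | 66.6% |
| Random 4/6 | about 6% | about 69% |
| Random 4/6/8 | about 2% | about 68% |

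A larger fixed block helps little with certain knowledge. Varying the size nearly removes it, but hardly changes the success of guessing.

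**5. Possible bias, on purely assumed inputs.** Suppose that 30% of patients are high risk with a 40% hernia risk and that overall risk is 25%. Low-risk patients then have (0.25 − 0.30 × 0.40)/0.70 = 18.6%. If every Duramesh slot that is known in advance waits for the next low-risk patient, expected risk in that arm falls by f × (25 − 18.6) points with no treatment effect, where f is the share known: 0.6 points at f = 10% and 2.1 at f = 33%. The planned difference is 15 points. Apart from the 25%, no input comes from the article, and the upper end needs perfect knowledge and universal avoidance.

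**The case against.** The best defence is that several conditions must hold together before anyone gains from the fixed block, and the article describes safeguards. Four stronger readings are tempting and are not supported.

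- **That one in three allocations are in fact known in advance.** This needs the whole stratum history and the block boundaries. A surgeon who sees only their own cases is certain of almost nothing. The article does not bar surgeons from sharing allocations with each other, but nothing shows that they do.
- **That surgeons offer participation to every patient.** They do so for emergencies only. The emergency share is not given, so the exposed fraction is unknown.
- **That unblinded research staff can follow the running sequence.** The article says that they handle randomisation. It does not say that they see past allocations across strata.
- **That patients could be selected on final extraction-site size or tissue quality.** Randomisation precedes the incision, so these can at most be anticipated.

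Consent on the day by the research team, late randomisation and the screening log also narrow the route. All of this limits the size of the concern, but it does not remove it. The surgeon performs the randomisation after consent in elective cases too, and the log does not cover the patients who matter most here. It is also fair to say that the remedy does little against someone who acts on a good guess.

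**Conclusion.** The point holds as a weakness of design that is cheap to remove. A single block size of 4, made public while recruitment was planned to be open, allows up to 33.3% of allocations to be deduced with certainty. That ceiling assumes complete knowledge of the stratum's earlier allocations and of the block boundaries; with partial knowledge the share is about k²/3. The exposure is greatest for emergency patients, where a consultant makes the offer and an unblinded consultant randomises. The statement that the web system secures concealment should be read with this limit. No misconduct is implied, and no size of bias can be derived from the article. Sample size, strata and analysis are unaffected.

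**What to change.** For the remaining recruitment, generate the unused part of the sequence with randomly varying block sizes, for example 4, 6 and 8, within the same four strata. Restrict knowledge of the sizes to the trial statistician and the web provider, do not publish them until recruitment closes, and state in the final report when the change was made.

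The cost is a regenerated list in the existing web system and a minor amendment. Maximum imbalance rises from 2 to 4 participants per stratum, so from 8 to 16 across the four strata in the worst case. The gain shrinks with each further patient randomised, so the change is best made promptly.
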